## Abstract

**Background:**

Genetic testing for risk of weight gain is already available over the internet despite uncertain benefits and concerns about adverse emotional or behavioral effects. Few studies have assessed the effect of adding genetic test feedback to weight control advice, even though one of the proposed applications of genetic testing is to stimulate preventive action. This study will investigate the motivational effect of adding genetic test feedback to simple weight control advice in a situation where weight gain is relatively common.

**Methods/design:**

First-year university students (n = 800) will be randomized to receive either 1) their personal genetic test result for a gene *(FTO)* related to weight gain susceptibility in addition to a leaflet with simple weight control advice (‘Feedback + Advice’ group, FA), or 2) only the leaflet containing simple weight control advice (‘Advice Only’ group, AO).

Motivation to avoid weight gain and active use of weight control strategies will be assessed one month after receipt of the leaflet with or without genetic test feedback. Weight and body fat will be measured at baseline and eight months follow-up. We will also assess short-term psychological reactions to the genetic test result. In addition, we will explore interactions between feedback condition and gene test status.

**Discussion:**

We hope to provide a first indication of the clinical utility of weight-related genetic test feedback in the prevention context.

**Trial registration:**

Current controlled trials ISRCTN91178663

## Background

‘Personalized’ healthcare aims to offer specific, targeted advice for disease prevention based on genetic risk status, [1,2]. Addition of information about genetic risk markers to standard care has been put forward as a way of empowering individuals to take responsibility for health maintenance, thereby maintaining quality of life and lowering healthcare costs [3]. To date, the clinical utility of most genetic risk markers is assumed to be low because of the small effect sizes of genes identified for ‘common’ conditions. However, genetic testing can already be purchased over the internet without involvement of healthcare providers (for example, http://www.23andme.com; http://www.deCODEme.com), suggesting that consumers are interested in this kind of information. The idea that genetic test feedback could promote behavior change is consistent with psychological theories (such as protection motivation theory [4]) that identify perceptions of risk as important for motivating risk-reducing actions. Within this model, however, a lower-risk genetic test result might reduce motivation. An alternative perspective is that ‘genetic determinism’ (the idea that genetic effects cannot be modified) could lead to a fatalistic attitude towards health maintenance for example, [5] in the case of a higher-risk result, whereas a lower-risk result could induce a false sense of immunity and complacency for example, [6]. Furthermore, there are concerns that individuals may discount their genetic result if it does not match their preconceived ideas about illness development [7]. To date, few studies have investigated the consequences of genetic test feedback for common conditions. One approach uses ‘vignettes’ in which people imagine receiving a genetic test result and anticipate their reactions. Results for smoking cessation and prevention of weight gain suggest that higher-risk feedback increases motivation to change behavior and does not appear to induce fatalism [8-10], while lower-risk feedback does not appear to induce complacency, and may even have a mildly motivating effect [9]. However, the gap between expressed intentions in the vignette context and actual behavior may be wide, so at best, these results only give an indication of the effects of actual test feedback.

‘Real’ genetic test feedback has received most attention in the smoking cessation field following the early discovery of genes coding for enzymes that reduce risk for lung cancer (*GSTM1* and *CYP2D6*). There has been evidence of increased motivation to quit following genetic test feedback [11,12], although a recent Cochrane review of five clinical studies failed to show any statistically significant effects on quitting when incorporating genetic feedback results into smoking cessation programs, either in the short term (two weeks), or in the longer term (six months) although study heterogeneity limited the interpretation of the results [13]. However, the physiological and psychological drivers of nicotine addiction make smoking cessation particularly difficult to achieve, and quit attempts are marked by frequent relapse [14]. Adding genetic test feedback in this context might be less influential than for other health promoting behaviors. The positive feature of these results was that there was no evidence that smokers receiving lower-risk results thought of themselves as immune to lung cancer for example, [12,15]. This corresponds with findings from vignette studies, and indicates that complacency may not be a major concern. There is some evidence that inclusion of genetic test feedback for risk of obesity into clinical care may be beneficial. Feedback on a gene implicated in weight gain (*bA3R*) resulted in increased motivation to lose weight in a small sample of obese individuals [16]. Another small qualitative study giving feedback on the *FTO* gene (also linked with weight gain), found that feedback increased motivation to lose weight ([name] and JW, unpublished). This study also found that the ‘scientific’ nature of the gene test result helped overweight participants feel less sense of personal failure and more confidence in managing their ‘condition’. A similar finding was reported in a community sample of overweight and obese adults, where genetic feedback reduced guilt and self-blame [17]. Raising awareness of the genetic etiology of obesity also helps minimize negative stereotyping by healthcare professionals [18].

Thus far, most research has centered on the reactions of already affected individuals, but a key proposed application for genetic feedback is *prevention* of ill health. The one study in this area analyzed responses to receiving results from a direct-to-consumer genetic test for a panel of diseases in over 2000 people who volunteered to be followed up in return for purchasing their test at a reduced rate [19]. Neither higher nor lower genetic risk for the panel of diseases was associated with changes in anxiety or health behaviors, nor were there changes in the number of health screening tests although intended use of health screening increased in the whole group. However, the participants in the study are likely to have been ‘early adopters’ of genetic testing who may be more health conscious than average and have less scope to change, supported by the fact that most of them were already following a low-fat diet. It is also possible that receiving results for a whole panel of diseases has a different effect from receiving results for a single condition because, inevitably, any high risk results are likely to be balanced by lower risk for others diseases, which may generate an overall null effect on risk perception. The present study will therefore investigate the impact of giving genetic risk feedback for a single condition, overweight, in conjunction with weight control advice, in a healthy, young adult sample entering a life stage where risk of weight gain is raised, to discover whether genetic feedback provides a ‘nudge’ toward unhealthy weight gain prevention. We will test the effect of adding feedback for the *FTO* gene, which has modest effects on weight gain and risk of obesity [20], to simple weight control advice. We use the university context because of evidence that first-year students have a high risk of weight gain (sometimes termed the ‘Freshman 15’ or ‘Freshman 5’) and low intentions to implement healthy behaviors [21,22].

### Study objectives and hypotheses

#### Primary research objective

The primary aim of the study is to test the hypothesis that adding genetic test feedback to weight gain prevention advice will result in higher motivation to prevent weight gain one month after receiving test feedback compared with receiving weight gain prevention advice alone.

#### Secondary research objectives

The secondary objectives are to assess differences in adherence to the advice and weight change from baseline to eight month follow-up in those receiving genetic test feedback and weight gain prevention advice compared with advice alone. We hypothesize that participants receiving genetic test feedback, regardless of risk status, will be more adherent to the advice and gain less weight over the study period than those receiving weight gain prevention advice alone. Within the group of participants receiving feedback and advice, we will also explore psychological reactions immediately after receiving genetic test feedback, and interactions between weight status and gene test status. We hypothesize that those receiving a higher-risk genetic test result will show higher negative affect but not higher fatalism in response to their genetic test result compared to those receiving an ‘average-risk’ genetic test result. We also predict that overweight participants receiving a ‘higher-risk’ result will value having an explanation for their weight more than normal weight participants, and that overweight participants will be more motivated to prevent further weight gain in response to a higher-risk genetic test result than those receiving an ‘average-risk’ result. All secondary objectives are exploratory, because of limited power.

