### Randomization

All consenting participants will be randomized to ‘FA’ (intervention) or ‘AO’ (control) after baseline data collection is complete and records have been anonymized using serial numbers. For group allocation, we will use the randomization function in the Statistical Package for Social Sciences (SPSS 19 for Windows®; SPSS Inc., Chicago, IL, USA), which randomly assigns a set percentage of cases to a specified number of groups. Each group will consist of 400 participants, and based on population frequencies of *FTO* we expect 252 to have at least one higher-risk (A) allele and 148 to have the lower-risk (TT) genotype. Randomization will take place after data collection of each wave is complete, but before the DNA analyses are conducted. Experimenter bias is unlikely, as records are anonymous and not easily identifiable. Although neither researchers nor participants will be blind to group allocation, follow-up weights will be measured objectively and print-out records kept, which excludes inadvertent manipulation of records. Questionnaire data will be collected online, which minimizes the risk of missing data or inadvertent manipulation.

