#### Secondary outcomes

Secondary outcomes are psychological reactions to genetic test feedback and actual behavior change as assessed by adherence to the individual weight control tips in the leaflet. Immediately after receiving genetic feedback (FA group after allocation, AO group after 8 months, see Figure 1), participants will complete a questionnaire concerning their psychological reactions using 18 items adapted from the vignette study by Meisel *et al*. [9]. One example is ‘Knowing my FTO gene test result provides me with an explanation for my body weight’ (strongly disagree to strongly agree).

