#### Secondary

Results from all secondary analyses will be considered as exploratory. One-way ANOVAs, followed by one-way ANCOVAs will be used to examine immediate psychological reactions to genetic test feedback in the sample overall once the AO group participants have received their genetic test results. Repeated-measures ANOVAs will be used to determine change in anthropometric measures within groups over time in the sample overall. Anthropometric differences between groups will be determined using one-way ANCOVA. Age, gender and baseline BMI will be included as covariates. Changes in diet quality, eating behavior and physical activity in the sample overall will be examined with repeated-measures ANOVAs. Changes between groups will be examined using one-way ANCOVAs, including age, gender and baseline BMI as covariates. Group differences in actual behavior change (as measured by adherence to the individual tips) will be assessed with a one-way ANCOVA. In addition, we will build an additive score of the total number of tips adhered to at least ‘occasionally’ and compare this in intervention and control group with a one-way ANCOVA. Age, gender and baseline BMI will be included as covariates. Bonferroni corrections will be used for multiple comparisons in all analyses. Within the ‘Feedback and Advice’ group, *FTO* status will be dichotomized into high/average risk, with those having at least one risk allele being classified as ‘higher-risk’. Ordinal regression analyses will be used to examine effects of risk status on motivation to control weight, as well as interactions between risk status and baseline BMI. Age and gender will also be included as predictor variables in the model. Finally, we will assess predictors of motivation to control weight with a multinomial regression analysis. We will include all potential predictors, including age, gender, *FTO* status, as well as stress, eating behavior, baseline BMI, and weight satisfaction.

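### The prediction that a higher-risk result does not raise fatalism is paired with Bonferroni-corrected difference tests, which cannot support it, and the population for the analysis is stated in two ways

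*Protocol article*

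**What the plan says.** Under *Secondary research objectives*, the article sets out to explore psychological reactions within the Feedback and Advice (FA) group. It predicts that those with a higher-risk result "will show higher negative affect but not higher fatalism in response to their genetic test result" than those with an average-risk result. The same section adds: "All secondary objectives are exploratory, because of limited power".

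*Secondary outcomes* says that reactions are measured immediately after feedback, "using 18 items adapted from the vignette study". FA participants answer after allocation. Advice Only (AO) participants answer after eight months, and the *Control group* section places their result after the follow-up body measurements are complete.

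*Statistical analyses, Secondary* states: "One-way ANOVAs, followed by one-way ANCOVAs will be used to examine immediate psychological reactions to genetic test feedback in the sample overall". That sentence goes on to say that this is done once AO participants have their results. The section also says "Bonferroni corrections will be used for multiple comparisons in all analyses" and "Results from all secondary analyses will be considered as exploratory". It gives no margin or interval criterion for fatalism and no number of comparisons for the correction.

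**The concern.** The prediction has two halves of opposite kind. Higher negative affect is a difference, and a difference test suits it. Fatalism being no higher is an absence of effect. The only outcome of an ANOVA or ANCOVA that agrees with it is a non-significant one, and small numbers or wide scatter produce that outcome just as well as a true absence does.

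Bonferroni normally guards against claiming too much. Here it works the other way: the stricter the threshold, the more often the predicted result appears, whether or not it is true.

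The population matters as well. The objective belongs to FA, but the analysis covers both arms. Pooling about doubles the numbers. It also mixes responses given after allocation with responses given at the end of the year, after the final weighing.

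The *Background* names fatalism as one of the worries about higher-risk results, so a weakly supported statement that it did not rise could carry weight beyond this trial.

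**Working it through.** The article gives no power, margin or precision figure for fatalism, so there is none to reproduce. Its sample size of 340 concerns the primary motivation outcome. The calculation below shows how often the planned type of test would miss a real rise.

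**Inputs from the article**
- Risk split per arm, from *Randomization*: "we expect 252 to have at least one higher-risk (A) allele and 148 to have the lower-risk (TT) genotype". Both arms together give 504 and 296.
- Loss: about half (*Minimizing drop out*) or 60% (*Sample size and assumptions*). Both describe follow-up. No figure is given for the immediate reaction questionnaire.
- 18 reaction items (*Secondary outcomes*).

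**Assumptions**
- The comparison is higher-risk against average-risk, two-sided.
- The true rise is 0.3 SD, chosen for illustration.
- Loss is 0%, 50% or 60%.
- The Bonferroni divisor m is 1 (no correction), 2 (negative affect and fatalism only) or 18 (each item tested, the worst case).

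**Formulas** (normal approximation, in SD units)
- SE = √(1/n₁ + 1/n₀)
- Chance of missing the rise = 1 − Φ(0.3/SE − z), with z = 1.960 for m = 1, 2.241 for m = 2 and 2.991 for m = 18

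| Population | n₁ v n₀ | SE | 0.3/SE | Missed, m = 1 | m = 2 | m = 18 |
|---|---|---|---|---|---|---|
| FA, complete | 252 v 148 | 0.104 | 2.90 | 17% | 26% | 54% |
| FA, 50% loss | 126 v 74 | 0.146 | 2.05 | 46% | 58% | 83% |
| FA, 60% loss | 101 v 59 | 0.164 | 1.83 | 55% | 66% | 88% |
| Pooled, complete | 504 v 296 | 0.073 | 4.10 | 2% | 3% | 13% |
| Pooled, 50% loss | 252 v 148 | 0.104 | 2.90 | 17% | 26% | 54% |
| Pooled, 60% loss | 202 v 118 | 0.116 | 2.59 | 26% | 36% | 66% |

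Worked example, FA at 60% loss: SE = √(1/100.8 + 1/59.2) = 0.164. With m = 1, Φ(1.83 − 1.96) = 0.45, so 55% are missed. With m = 18, Φ(1.83 − 2.99) = 0.12, so 88% are missed.

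In every row, moving from m = 1 to m = 18 raises the chance of the predicted result while the true rise stays the same.

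**What an interval rule would achieve.** Suppose *not higher* is claimed only if the upper limit of the 90% confidence interval lies below 0.3 SD (illustrative). With no true difference, the chance of success is Φ(0.3/SE − 1.645). At 60% loss:
- pooled: Φ(2.59 − 1.645) = 0.83
- FA alone: Φ(1.83 − 1.645) = 0.57

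With a 95% interval, 1.960 replaces 1.645 and the figures fall to about 74% and 45%.

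**The case against.** The strongest reply is that the article already limits these results. It calls the secondary objectives exploratory and gives limited power as the reason, in the same section as the prediction. It states no rule that non-significance will count as proof of no harm, and a significant rise would refute the prediction. This stands, and it lowers the severity. It does not cure the mismatch: admitted low power makes a non-significant result less informative about absence, not more.

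The size depends on assumptions. The divisor is not stated, and nothing says that all 18 items are tested separately. The questionnaire follows immediately after feedback, so loss could be well below the follow-up figures. Both objections stand, which is why ranges are shown.

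A condensed article may also leave model terms and interval criteria to an analysis plan that is not shown. That is fair for an arm term, whose absence here is only silence. It does not cover the blanket Bonferroni rule or the conflicting populations, because the article states both outright.

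**Conclusion.** The point holds in a limited form. The stated tests cannot support the prediction of no higher fatalism, the stated correction favours that prediction, and the two sections disagree on who is analysed. With the assumed 0.3 SD rise and 0% to 60% loss, the chance of missing it is 17% to 55% in FA and 2% to 26% pooled at the 5% level. With the worst-case divisor of 18 it is 54% to 88% and 13% to 66%.

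A reader might go further on three counts that the article does not support:
- **That the trial is set to declare no harm from a non-significant test.** This is an inference from the form of the prediction, not a stated rule.
- **That a meaningful rise would probably be missed.** Pooled without correction, at most 26% are missed in these scenarios. A miss rate above one half needs FA alone with heavy loss, or a large divisor. That 0.3 SD is meaningful is itself an assumption.
- **That fatalism is the main feared harm.** The *Background* lists it beside complacency and discounting of the result, and does not rank them.

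**What to change.** - Report the higher-risk minus average-risk difference in fatalism with its unadjusted confidence interval, and exempt this claim from Bonferroni.
- State *not higher* only if the upper limit lies below a margin that the investigators set in advance and justify. Otherwise call the result inconclusive. The 0.3 SD used above is only an illustration, since the article gives no margin.
- Reconcile *Secondary research objectives* with *Statistical analyses, Secondary* on the population. If the arms are pooled, include arm, which also carries the timing of feedback, in the model.

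This needs changed wording and one justified margin, and no extra participants. The cost is that *not higher* becomes harder to claim. With the illustrative margin, a 90% interval, 60% loss and no true difference, the claim would succeed about 83% of the time pooled but only about 57% in FA alone.

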## Methods/design

### Study design

The design will be an open, two-arm, individually-randomized, controlled trial comparing the effects of genetic test feedback for risk of weight gain combined with weight control advice (FA) with a control condition of giving weight control advice only (AO). The control group will receive their genetic test result at the end of the study. A summary of the study procedures is shown in Figure 1. Participants consenting to take part in the study will be randomized and offered the following:

**Figure 1 F1:**
[figure not shown]
Flowchart of study procedures.

#### Intervention group (‘Feedback and Advice’ group)

Following baseline measurements, participants randomized to the ‘Feedback and Advice’ group will receive their gene test result in an email, as used by internet-based genetic testing services. This format was used in a previous study ([name] and JW, unpublished) and found acceptable to participants. The result letter will be sent as an email attachment so that participants can open and read it at a convenient time. The letter will contain the personal result in addition to information about prevalence in the population. The email will also include a short information leaflet written in simple language, giving a brief overview about the *FTO* gene, its mode of inheritance, and magnitude of influence on body weight. Contact details of the research team will be included for questions about the test results. The *FTO* information leaflet and the result letter were piloted in a general population sample that included both men and women of various ages and ethnicities (n = 35), and has been used in previous work ([name] and JW, unpublished). Both were deemed informative, comprehensive and easy to understand. Readability was assessed with the Flesch Reading Ease formula and the Flesch-Kincaid Grade Level formula, and letter and leaflet received a score of 71.0 and 67.0 respectively, which translates to the reading level expected in grade 6 (age 12). Participants will also receive weight control advice in the form of a short leaflet containing practical ‘tips’ on how to avoid weight change when starting university. The format and design is based on habit formation model [23], and is currently being evaluated in a large population-based sample [24]. Readability of the leaflet was tested with the Flesch Reading Ease formula and the Flesch-Kincaid Grade Level formula, and found to be high (71.1), comparable to the reading level expected in grade 6 (age 12).

